### Strategies to improve adherence to interventions {11c}

Patients in the intervention group will receive, throughout the year, notifications in the app to promote their adherence to the intervention.

The control group will receive a phone call 1 week after the group sessions to promote adherence to the intervention.

Both groups will receive a book on healthy nutrition and lifestyle developed by the Dutch cooperation of dieticians as an incentive. This book provides additional information on a healthy lifestyle beyond the group sessions and the information in the app.

### Relevant concomitant care permitted or prohibited during the trial {11d}

Patients will receive their usual medical care and are allowed to use all their prescribed medication. Anti-diabetic medication will be adjusted before the start of the intervention, according to the guideline demedicalisation for T2D [19]. Furthermore, medication is individually adjusted when hypo- or hyperglycaemia do often occur. Other medications such as antihypertensive medication will be adjusted as required and always in agreement with the medical team. No concomitant care will be prohibited during the study.

### Provisions for post-trial care {30}

After finishing the study, patients will continue receiving their usual diabetes treatment, including dietary treatment.

### Outcomes {12}

Main study parameters are as follows:Difference in weight (% change) between the control and intervention group after 1 year. Weight will be measured, after removal of shoes using a Seca 888 compact digital flat scaleDifference in costs will be determined by the difference in costs of the treatment, as well as costs of health care and costs of production losses, measured by the Trimbos/iMTA Questionnaire for Costs (TiC-P) [20]

Secondary study parameters are as follows:Quality of life, measured with the EuroQol questionnaire EQ-5D-5L [21]Diabetes regulation measured by HbA1c (mmol/mol) via routine laboratory procedures

Other study parameters are as follows:Cardiovascular risk factors: blood pressure (mmHg), total cholesterol (mmol/l), LDL cholesterol (mmol/l), HDL cholesterol (mmol/l), triglycerides (mmol/l), fasting blood glucose (mmol/l), all measured via routine clinical care/lab

### Participant timeline {13}

The participant timeline is presented in Table 1.

**Table 1 Tab1:** Schedule of enrolment, interventions, and assessments

	**Study period**						
	**Enrolment**	**Allocation**	**Post-allocation**				**Close-out**
**Timepoint**	***-T***_***1***_	**0**	***T***_***0***_ *Start*	***T***_***1***_ *Week 10*	***T***_***2***_ *Week 20*	***T***_***3***_ *Week 30*	***T***_***4***_ *Week 52*
**Enrolment:**							
Eligibility screen	X						
Informed consent	X						
Discuss in multidisciplinary consultation	X						
Allocation		X					
**Study visits:**							
E-VLED			X		X		X
VLED			X	X	X	X	X
**Assessments:**							
Laboratory measurement venipuncture			X	X	X		X
Biobank vena punction			X	X	X		X
Length			X				
Waist circumference			X	X	X		X
Body composition			X	X			X
Resting energy expenditure			X	X			X
Dietary history			X	X			X
Physical activity			X	X	X		X
Questionnaire about demographic variables, lifestyle and medication use			X	X	X		X
EQ-5D-5L			X	X	X		X
DTSQ			X	X	X		X
EHIQ			X	X	X		X
HADS			X	X	X		X
Weight			X	X	X		X
TiC-P			X	X	X		X

### Sample size {14}

In our previous study using the same diet intervention [5], the standard deviation of the difference in weight loss at 12 months was 7.58 kg, and the baseline weight was 105 kg; thus, the standard deviation percentage weight loss was 7.2%. In the field of long-term weight loss, two weight loss percentages are considered clinically relevant, 3% and 5% [22–24]. In order to stay on the safe side, we choose the non-inferiority margin based on the lower of these two percentages, i.e. a non-inferiority margin of 3%. Results of recently published randomised controlled trials on dietary eHealth interventions [25, 26] have yielded estimates for the percentage weight loss due to these interventions. In light of these results, we assumed in the power analysis that the weight loss percentage is 2% greater in the intervention arm than in the control arm. This estimate of 2% was obtained by averaging the results of Katula et al. (− 3.4%) and Baer et al. (1.1%). Based on a one-sided alpha of 0.025, power set at 0.80, we calculated that at least 33 participants in each study group are required for the present study (calculated using R). Anticipating a drop-out of 20%, based on attrition data of the POWER study, we aim for the inclusion of 80 participants (40 participants per group).

### Recruitment {15}

Patients will be recruited from the outpatient diabetes clinic of the University Medical centre, Erasmus MC in Rotterdam, the Ikazia Hospital in Rotterdam and dietician practice HRC in Rotterdam by the researcher, based on the inclusion and exclusion criteria. Patients interested in participating in the study will receive the patient information letter by the coordinating researcher. If the patient is still interested in participating, a telephone consultation is scheduled in which the investigator will check eligibility and patients will have the opportunity to ask their questions about the study. After the patient signs the informed consent form, the appointment for the baseline measurements will be set up, and the participant will be allocated to the control or intervention group, and receive information on the first kick-off group meeting.

### Assignment of interventions: allocation

#### Sequence generation {16a}

Eligible patients who signed informed consent will be randomly assigned to either the intervention group or the control group in groups of ten patients. This means that patients who have given informed consent will be randomised only when a group of ten patients is reached, who will then all be in the same treatment group. The 8 groups of ten patients will be randomised with an allocation ratio of 1:1, using blocked randomisation with stratification by centre. The initial block size per centre is two groups (i.e. 10 patients per randomisation arm), and in two of the three centres, there will be a second block of one group. The randomisation, according to a random block design stratified to study site, is supervised by JR and is blinded for the researcher/dietician recruiting and/or performing the intervention. The randomisation is computer controlled.

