### Trial design {8}

This study is a randomised, controlled, non-inferiority multi-centre trial with a duration of 1 year. After signing informed consent, eligible participants will be randomised 1:1 to the intervention (E-VLED) or control (VLED) group. Outcome parameters will be measured at baseline, 2 months, 4 months, and at 1 year. In Fig. 1, we show the flow chart of this study.

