### Statistical methods

#### Statistical methods for primary and secondary outcomes {20a}

All analyses will be conducted according to the intention-to-treat principle. Normality of the data and homogeneity of variances will be tested using Shapiro–Wilk test and Levene’s test. As measures of central tendency for numerical data, we will use the mean (in case of normal distribution) and median values (in case of non-normal distribution), with respectively the standard deviation and interquartile range as measures of dispersion.

The primary endpoint will be defined as the between group difference in relative weight change during 12 months. The relative weight change will be analysed with a general linear model for repeated measurements, with independent variables treatment arm, time point (T1, T2, or T3), hospital, and the interaction between treatment arm and time point. The within patient correlations will be modelled using an unstructured covariance matrix. The estimated difference between treatment arms (intervention minus control) in the relative weight change at T3 (12 months) will be calculated using the estimated marginal means. Non-inferiority will be concluded if the upper limit of the 95% confidence interval of this estimated difference remains below the stated non-inferiority margin of 3.0%. When non-inferiority has been demonstrated, the costs and effects will be expressed in the savings per percent weight reduction/patients who successfully lost weight, by means of a probabilistic model, so that the likely skewed data on costs can be considered.

For the secondary analyses of the efficacy outcomes cardiovascular risk factors (lipids), quality of life (EQ-5L), patient satisfaction (DTSQ), attrition (drop-out), and compliance (log-on information and kcal intake vs advised), we will use analysis of covariance (ANCOVA) models. The dependent variable in these models will be the outcome at T1, T2, or T3, and the independent variables will be treatment arm, the outcome at baseline (T0), and hospital. The secondary analyses are exploratory in nature as the power calculation is based on the primary outcome.

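### Whole groups of ten are randomised, but the sample size and primary model treat patients as independent: any positive within-group correlation makes the interval too narrow, and eight groups do not give 80% power

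*Protocol article*

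**What the plan says.** All references are to the protocol article.

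- **Randomisation.** Sequence generation {16a} states that patients are "randomised only when a group of ten patients is reached, who will then all be in the same treatment group", and then: "The 8 groups of ten patients will be randomised with an allocation ratio of 1:1, using blocked randomisation with stratification by centre". Each of the three centres has a first block of two groups, and two centres have one further group, which gives 2, 3 and 3 groups. Sections {16b} and {16c} confirm that one allocation is issued per completed group.
- **Design label.** Trial design {8} says that "eligible participants will be randomised 1:1 to the intervention (E-VLED) or control (VLED) group" and does not mention groups.
- **Sample size.** Section {14} uses "Based on a one-sided alpha of 0.025, power set at 0.80" and reports that "we calculated that at least 33 participants in each study group are required for the present study". It states no ICC and no design effect.
- **Primary model.** Section {20a} sets out a repeated-measures linear model and lists its terms as follows: "with independent variables treatment arm, time point (T1, T2, or T3), hospital, and the interaction between treatment arm and time point". On correlation it says: "The within patient correlations will be modelled using an unstructured covariance matrix".

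**The concern.** The unit that receives an allocation is the group, so the comparison between arms is a comparison between about four groups and four groups. Patients in a group are brought together before allocation and begin with a kick-off group meeting. The control arm has five group meetings, in which motivation and goal setting are followed up, and the intervention arm has three. Group dynamics, calendar period and the dietician can all make outcomes within a group more alike.

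The primary model allows for repeated measures on one patient but not for likeness between patients of one group. The hospital term does not replace a group term: each centre has two or three groups, and the arms are compared between groups within a centre.

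The direction of the error matters in a non-inferiority trial. Too small a standard error pulls the upper confidence limit down, towards the conclusion the trial hopes to reach. The cost-per-effect analysis is then triggered by that same conclusion.

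**Working it through.** **Inputs from the article.** SD of percentage weight change 7.2 (7.58/105); margin from "a non-inferiority margin of 3" per cent; assumed advantage of 2 points for the intervention, so the distance to the margin is 3 + 2 = 5; one-sided alpha 0.025; power 0.80; 40 included per arm with 20% drop-out. That leaves 40 × 0.8 = 32 evaluable per arm, or 8 in each of four groups.

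**Assumption.** The article gives no ICC. The range 0 to 0.20 is assumed, with the same value in both arms.

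**1. The stated figure.** For independent patients, n = 2 × [7.2 × (1.960 + 0.842)/5]² = 32.55, rounded up to 33. This matches {14} and corresponds to a design effect of exactly 1.

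**2. The interval under the planned model.** With 8 evaluable patients per group, the design effect is DE = 1 + (8 − 1) × ICC. The planned standard error is too small by a factor √DE. The one-sided error at a true difference of +3 is then 1 − Φ(1.960/√DE), and the coverage of the nominal 95% interval is 1 minus twice that error.

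| ICC | DE | √DE | Coverage | One-sided error, formula | Same, simulated |
|---|---|---|---|---|---|
| 0 | 1.00 | 1.00 | 95% | 2.5% | 2.4% |
| 0.01 | 1.07 | 1.03 | 94% | 2.9% | 2.8% |
| 0.05 | 1.35 | 1.16 | 91% | 4.6% | 4.6% |
| 0.10 | 1.70 | 1.30 | 87% | 6.6% | 7.0% |
| 0.20 | 2.40 | 1.55 | 79% | 10.3% | 11.1% |

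The simulation used 40,000 runs, centres with 2, 3 and 3 groups, 8 patients per group, and patient-level regression of the 12-month outcome on arm and centre. It shows that the hospital term does not cure the problem. It is a one-time-point stand-in for the repeated-measures model.

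**3. Power when the eight groups are respected.** The variance of a group mean is V = 7.2² × [ICC + (1 − ICC)/8].

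- *Ignoring centre:* SE = √(0.5 × V), with 8 − 2 = 6 df.
- *Adjusting for centre:* with splits of 1:1, 1:2 and 2:1 within centres, SE = √(V / (1/2 + 2/3 + 2/3)) = √(0.545 × V), with 8 − 4 = 4 df.

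Power comes from the noncentral t distribution with noncentrality 5/SE. For example, at ICC 0.10 adjusted for centre, SE = 2.45, noncentrality = 2.04 and power = 35%.

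| ICC | SE, 6 df | Normal approximation | 6 df, no centre | 4 df, with centre (simulated) |
|---|---|---|---|---|
| 0 | 1.80 | 79% | 64% | 52% |
| 0.01 | 1.86 | 77% | 61% | 50% |
| 0.05 | 2.09 | 67% | 52% | 41% |
| 0.10 | 2.35 | 57% | 43% | 35% |
| 0.20 | 2.79 | 43% | 33% | 26% |

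In the same simulation the 4-df group-level analysis kept its one-sided error between 2.3% and 2.7% at every ICC tried.

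**4. Groups needed for 80% power.** With 8 evaluable per group, k groups per arm and 2(k − 1) df, the requirement is 6 per arm (120 patients) at ICC 0.01, 7 (140) at 0.05, 9 (180) at 0.10 and 11 (220) at 0.20. The plan has four per arm (80 patients).

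**The case against.** The strongest reply is that the harm depends on a quantity nobody has stated. At an ICC of exactly zero the planned interval is correct, and power with 32 evaluable per arm is about 79%. At 0.01 the standard error is short by only 3%. The correlation may also be lower in the intervention arm, which meets less often. All of this is true, and it is why the claim about the interval is conditional on a positive ICC. It does not rescue the plan: no zero-ICC assumption is stated, and eight groups are too few to demonstrate one.

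A second point also stands. At low ICC most of the power loss comes from the few degrees of freedom, not from correlation: at ICC 0 power is already 64% on 6 df and 52% on 4 df with centre. That is the price of randomising eight units, and a power statement for this design has to include it.

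Third, a random intercept can break down with so few groups. With 4 and 56 df, the moment estimate of the between-group variance is zero or negative in about 54% of trials at ICC 0.01 and 41% at 0.05. If it is truncated at zero, the interval may fall back towards the planned one. This bears on how the fix is written, not on whether one is needed.

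Finally, the article does not say in so many words that each randomised ten forms one meeting group; the kick-off meeting that follows allocation makes it likely. The point cannot be left to an analysis plan, because the sample size, the model terms and the correlation structure are all stated and all omit the group.

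**Conclusion.** The concern holds. The design is a cluster-randomised trial with eight groups, stratified by centre, but it is powered and analysed as 80 independent patients. For any positive ICC the planned interval is too narrow, in the direction that favours a non-inferiority claim. At assumed ICCs of 0.05 to 0.10 the false-claim rate is about two to three times the nominal 2.5%; at 0.01 the excess is small. The stated 80% power is correct arithmetic for a design that is not used. A centre-adjusted analysis based on the eight groups has about 52% power at ICC 0 and 50% to 35% for ICC 0.01 to 0.10. These figures rest on the article's SD, margin and assumed 2-point advantage, 8 evaluable patients per group, and an equal ICC in both arms. Because the primary conclusion is affected, this must be corrected before the data are analysed.

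**What to change.** 1. In {8} and {16a}, call the trial cluster-randomised with the group of ten as the unit, and keep the group identifier in the analysis data.
2. In {20a}, name one primary analysis. Either add a random intercept for randomisation group to the repeated-measures model with a small-sample correction such as Kenward–Roger, or use a group-level t-analysis adjusted for centre. If the random intercept is chosen, state in advance what happens when the between-group variance is estimated as zero. The other analysis can serve as a sensitivity analysis.
3. Carry the group effect into the secondary ANCOVA models and the sex and ethnicity interaction models. In the cost analysis, resample whole groups rather than patients.
4. In {14}, state the assumed ICC with a range, and restate the power for eight groups of ten.

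The cost is changed analysis wording and a restated power figure, with no new visits or patients. The confidence interval will be wider and the stated power lower. The change makes the inference valid but does not restore 80% power, which would need the additional groups shown in the working.

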### Assignment of interventions: blinding

#### Who will be blinded {17a}

Given the nature of the intervention, the participants could not be blinded. Due to practical reasons, we elected not to blind investigators and medical staff. However, the first preliminary statistical analyses of the primary outcome will be performed by an independent statistician, blinded to the allocation.

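### The arm of each centre's second group can be deduced before its patients are recruited, 40 per arm is not guaranteed, and Table 1 puts baseline after allocation

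*Protocol article*

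**What the plan says.** Sequence generation {16a} waits until ten consenting patients are available and then puts all ten in one arm. There are eight such groups, allocated 1:1 in blocks stratified by centre. On block size it says "The initial block size per centre is two groups (i.e. 10 patients per randomisation arm") and adds that "in two of the three centres, there will be a second block of one group". The same section says that the randomisation "is blinded for the researcher/dietician recruiting and/or performing the intervention".

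Concealment mechanism {16b} and Implementation {16c} keep the list with a secretariat. Once a group of ten is complete, the investigator or researcher phones, is told the arm, and then enrols that group. Under Recruitment {15} it is the researcher who recruits. Who will be blinded {17a} says that "we elected not to blind investigators and medical staff".

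On the timing of baseline, {15} says that after consent "the appointment for the baseline measurements will be set up, and the participant will be allocated to the control or intervention group". Table 1 has an allocation column (timepoint 0) followed by T0. T0 falls under the post-allocation heading and carries the first weight, EQ-5D-5L and DTSQ. Sample size {14} aims for 80 participants, 40 per group.

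**The concern.** Three features of the allocation procedure deserve attention.

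- **Predictability.** A block of two groups with one per arm leaves nothing to chance once the first group's arm is known. The person who learns that arm is also the person who recruits the next ten patients. Keeping the list with a secretariat does not prevent this, because the arm follows by deduction. A recruiter could then, even without intent, favour motivated or app-minded patients for one arm. In a non-inferiority trial, selection that favours the app arm pushes towards the claim the trial hopes to make, and no later analysis fully removes it.
- **Balance.** A block of one group cannot be balanced, so the stated 1:1 ratio and 40 per group need a further rule that the text does not give.
- **Baseline after allocation.** If T0 follows allocation, the weight from which relative weight change is calculated is recorded when staff and patients can know the arm. So are the baseline values of EQ-5D-5L and DTSQ, which Statistical methods {20a} uses as covariates in the exploratory ANCOVA models. Patients may also leave between allocation and T0.

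**Working it through.** **1. The plan's own sample size.** Inputs from Sample size {14}: "Based on a one-sided alpha of 0.025, power set at 0.80"; "the standard deviation percentage weight loss was 7.2"%; "a non-inferiority margin of 3"%; and an assumed true advantage of 2% for the intervention. The distance to the margin is 3 + 2 = 5.

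n per arm = 2 × (7.2/5)² × (1.960 + 0.842)² = 2 × 2.0736 × 7.849 = 32.6, rounded up to 33. The stated 33 is reproduced. With 40 per arm and 20% drop-out, 40 × 0.8 = 32 per arm remain.

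**2. Block count.** Three centres × 2 groups + two centres × 1 group = 8 groups = 80 patients, as stated.

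**3. Groups whose arm can be deduced in advance.**
- First group in each centre: arm unknown until ten have consented (3 groups).
- Second group in each centre: must be the opposite arm (3 groups, 30 of 80 patients, 37.5%).
- Single-group blocks: unknown until the call if drawn independently (2 groups).

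This assumes that the recruiter knows the block size, which the article publishes, and that groups at a centre fill in sequence, which the ten-at-a-time phone procedure implies.

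**4. Arm totals.** The three two-group blocks fix 30:30. If the two single-group blocks are independent fair draws:
- opposite arms, 40:40: 2 × 0.5 × 0.5 = 0.50;
- both intervention, 50:30: 0.25;
- both control, 30:50: 0.25.

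Whatever the draw, each centre with a third group ends 20:10 or 10:20.

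**5. Power after 20% drop-out**, treating patients as independent as the plan does. SE = 7.2 × √(1/n₁ + 1/n₂); power = Φ(5/SE − 1.96).
- 32:32: SE = 1.800, 5/SE = 2.778, power 0.793 (noncentral t 0.781).
- 40:24: SE = 1.859, 5/SE = 2.690, power 0.767 (noncentral t 0.754).

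The loss is about 2.6 percentage points.

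**6. Two repairs that look natural but do not help.**
- Forcing the two single groups into opposite arms guarantees 40:40, but up to 4 of 8 groups (40 of 80 patients) then become predictable to anyone who knows the rule.
- One overall list of four groups per arm has 70 possible sequences. With centres of 3, 3 and 2 groups, every centre has both arms in 2 × (3×3 + 3×3) = 36 of them. In the other 34 (49%) at least one centre has a single arm, and a centre term cannot recover a within-centre comparison there.

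**7. Timing of baseline.** Table 1 puts allocation before T0. Recruitment {15} mentions the appointment for baseline and then allocation, but does not say whether the measurements themselves come first. Only Table 1 settles the order.

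**The case against.** A reader might infer that concealment fails for the whole trial. The documents do not support that. First groups are concealed until ten patients have consented, and so are the single groups if drawn independently. The blinding statement can fairly be read as describing the list, which the secretariat does hold. That is a reason to narrow the statement; as written it names the recruiter and does not hold for the second groups.

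A reader might also conclude that 40 per group will not be reached, or that a 50:30 split has an unconditional chance of one half. Neither follows. Forty per group is an aim, and 1:1 for the eight groups is compatible with single groups placed in opposite arms. The article does not say which was done. The 0.50 holds only for independent draws.

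The effect on power is small, and the documents allow no estimate of the size of selection bias. Sequential filling is implied rather than stated.

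On baseline, weight is read from a digital scale and is less open to influence than a questionnaire. The primary model has no baseline covariate, and the ANCOVA models are called exploratory. HADS is collected at T0 but is not among the outcomes listed for ANCOVA, so no covariate argument extends to it. Even so, T0 weight remains the reference for the primary endpoint.

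Finally, Trial status gives July 2023 as the estimated end of recruitment and the article appeared in October 2023, so changes to procedure may come too late for most groups. Reporting and correction of the text remain possible.

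**Conclusion.** The point holds in limited form. The second group's arm in each centre (3 of 8 groups, 30 of 80 patients) can be deduced before recruitment, provided groups fill in sequence and the recruiter knows the published block size. That contradicts the statement that the randomisation is blinded for the recruiter. The main risk is selection bias, whose size cannot be calculated from the documents.

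Forty per arm is not guaranteed by the scheme as written. Under independent draws it occurs with probability 0.50, and the alternative costs little power (noncentral t, 0.78 to 0.75). The order in Table 1 is a separate weakness: it causes neither the predictability nor the imbalance, but it leaves the reference weight and the EQ-5D-5L and DTSQ baselines open to knowledge of the arm. The text should be corrected; the trial is not invalidated.

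**What to change.** 1. Complete all T0 measurements and questionnaires for a group before the allocation call, and align Table 1 and Recruitment {15} with that order. This changes the visit order only and costs almost nothing.
2. Restrict the blinding statement in {16a} to the list itself, and state that the second group's arm in each centre is predictable. This is a text change.
3. For groups not yet recruited, fix the time-ordered invitation list for both groups of a block before the first allocation is requested, and log refusals. This may slow recruitment, which the Discussion already expects to lag.
4. For groups already recruited, report the predictability and show baseline characteristics by first and second group within block. This needs one extra table.
5. State how the two single-group blocks were drawn. If independently, describe 40 per group as expected rather than fixed.

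Neither a joined cross-centre block nor a single overall list is recommended, for the reasons in step 6 of the working.
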